## Abstract

**Background:**

The SARS-CoV-2 pandemic is a global threat affecting 210 countries, with 2,177,469 confirmed cases and 6.67% case fatality rate as of April 16, 2020. In Africa, 17,243 cases have been confirmed, but many remain undiagnosed due to limited laboratory-capacity, suboptimal performance of used molecular-assays (~30% false negative, Yu *et al*. and Zhao *et al*., 2020) and limited WHO-recommended rapid-tests.

**Objectives:**

We aim to implement measures to minimize risks for COVID-19 in Cameroon, putting together multidisciplinary highly-experienced virologists, immunologists, bioinformaticians and clinicians, to achieve the following objectives: (a) to integrate/improve available-infrastructure, methodologies, and expertise on COVID-19. For this purpose, we will create a platform enabling researchers/clinicians to better integrate and translate evidence into the COVID-19 clinical-practice; (b) to enhance capacities in Cameroon for screening/detecting individuals with high-risks of COVID-19, by setting-up effective core-facilities on-site; (c) to validate point-of-care SARS-CoV-2 molecular assays allowing same-day result delivery, thus permitting timely diagnosis, treatment, and retention in care of COVID-19 patients; (d) to implement SARS-CoV-2 diagnosis with innovative/highly sensitive ddPCR-based assays and viral genetic characterization; (e) to validate serological assays to identify COVID-19-exposed persons and follow-up of convalescents.

**Methods:**

This is a prospective, observational study conducted among COVID-19 suspects/contacts during 24 months in Cameroon. Following consecutive sampling of 1,536 individuals, oro/nasopharyngeal swabs and sera will be collected. Well characterised biorepositories will be established locally; molecular testing will be performed on conventional real-time qPCR, point-of-care GeneXpert, antigen-tests and digital droplet PCR (ddPCR); SARS-CoV2 amplicons will be sequenced; serological testing will be performed using ELISA, and antibody-based kits. Sensitivity, specificity, positive- and negative-predictive values will be evaluated.

**Expected outcomes:**

These efforts will contribute in creating the technical and clinical environment to facilitate earlier detection of Sars-CoV-2 in Africa in general and in Cameroon in particular. Specifically, the goals will be: (a) to implement technology transfer for capacity-building on conventional and point-of-care molecular assays, achieving a desirable performance for clinical diagnosis of SARS-CoV2; (b) to integrate/improve the available infrastructure, methodologies, and expertise on Sars-CoV2 detection; (c) to improve the turn-around-time for diagnosing COVID-19 infection with obvious advantage for patients/clinical management thanks to low-cost assays, thus permitting timely treatment and retention in care; (d) to assess the epidemiology of COVID-19 and circulating-variants in Cameroon as compared to strains found in other countries.

## Introduction

### Background and rationale

#### The unprecedented spread of coronavirus worldwide and in sub-Saharan Africa in particular, calls for an urgent and coordinated continental response

Three and half months after notification of the first cases of pneumonia related to coronavirus disease in December 2019 (COVID-19) in Wuhan, 210 countries have been affected worldwide for a total of 2,177,469 confirmed cases, with about 19% morbidity (12% mere and 5% severe), a case fatality rate (CFR) of 6.67% (145,304) and a poor recovery of 25.11% (546,475) as of April 16, 2020 [1, 2]. The number of confirmed cases and CFR range respectively from 748,256 and 4.77% (35,688) in the Americas to 17,243 and 5.28% (911) in Africa, with a declining CRF over time [2]. However, the level of risk is postulated to be much more higher in sub-Saharan Africa (SSA) owing to the weak quality of healthcare and surveillance systems. Interestingly, SSA was the last continent where infected cases were reported (partly due to limited diagnostic potentials); the numbers of circulating SARS-CoV-2 cases might be under-reported; and consequently the burden of COVID-19 might be largely under-estimated in terms of morbidity/mortality (due to suboptimal health care systems) and socio-economic impairements. Thus, evidence-based decision-making are needed for timely public health responses [2, 3].

Though Africa currently appears with the lowest number of COVID-19 confirmed cases, the outbreak is propagating very fast throughout the continent [3]. African males are more affected than women (3/2 M/F ratio), median age is 41 (min-max: 0–88) years, and older males are disproportionately affected [3]. As one of the African countries with high incidence of COVID-19 in Central-Africa, Cameroon has in 2020 reported 1,016 cases out of 4,982 tested [4]. This therefore suggests the need of a coordinated response strategy from country-level to other SSA countries [3, 4], and calls for a large scale and early SARS-CoV-2 detection approach in order to mitigate COVID-19 associated-impairements within the SSA settings.

#### Molecular diagnostics of SARS-CoV-2 deserve adapted strategies to limit false reporting

The viral nucleic acid real-time reverse transcription-polymerase chain reaction (rRT-PCR) assay has become the current standard for the molecular diagnosis of COVID-19. However, there are limitations in the global supply, technical challenges in testing thousands of samples daily, high demands for the rRT-PCR primers, lengthly turnaround times, and varying sensitivities of invitro diagnostic assays. Due to these limitations, the field implementation of rRT-PCR remained suboptimal regarding the need for rapid and simple screening of COVID-19 infected individuals [5].

Regarding rRT-PCR detection of SARS-CoV-2 in different types of clinical specimens, bronchoalveolar lavage fluids yielded the highest positivity (93%), followed by sputum (72%), nasal swabs (63%), fibrobronchoscope brush biopsy (46%), pharyngeal swabs (32%), feces (29%), blood (1%) and urine (0%). Moreover, except for the nasal swab specimen reported with a mean PCR cycle-threshold value of 24.3 (1.4 × 10^6^ copies/mL), the mean cycle-threshold values of all other specimen types were greater than 30 (<2.6 × 10^4^ copies/mL), suggesting varying viral shedding according to specimens and the need for combining specimen types for improved diagnostic sensitivity [6]. Using an N-gene specific quantitative RT-PCR assay, viral loads in throat swab and sputum peaked around 5–6 days after symptoms onset, ranging from 104 to 107 copies per mL [7, 8]. In contrast, Xi *et al*. showed a peak of infectiousness at 0–2 days before symptom onset [9]. These observations suggest discrepancy in understanding the optimal timing for SARS-CoV2 testing and the need for further investigations [8, 9]. Of note, median duration of SARS-CoV-2 RNA shedding appears around 12, 18 and 19 days after symptoms onset in nasopharyngeal swabs, stools and sputum respectively [10–12]. Regarding disease severity, the mean viremia of severe cases was significantly higher than that of mild cases, suggesting that higher viremia is a predictor of severe/critical outcomes [10, 13]. This is likely true as 90% of mild cases become negative on RT-PCR by day 10 post-onset of symptoms while most severe/critical cases remain positive after 10 days of COVID-19 post-symptom onset [11]. The U.S FDA granted Emergency Use Authorization (EUA) for PCR equipment for SARS-CoV-2 testing, of which: (1) Da AN Gen SARS-CoV-2 (Sun Yat-sen University); (2) Abbott Real Time SARS-COV-2 (Abbott Molecular); (3) Xpert Xpress SARS-COV-2 Test (Cepheid), and (4) Panther Fusion SARS-COV-2 (Hologic Inc.). Among these assays, the Xpert revealed satisfactory positive (99.5%) and negative (95.8%) agreements for SARS-CoV-2 detection in a variety of upper- and lower-respiratory-tract specimens. Its high sensitivity, short time-around-time (45 min) and simple procedure even for non-laboratorians, the Xpert would be helpful in case of clinical emergency [14]. In this context, deploying such device through mobile laboratories equipped with appropriate biocontainment may contribute substantially in the pandemic control (i.e. active case finding of tuberculosis among high-risk targets in South Africa) [15]. Thus, applying these concepts in SSA will be of great relevance in defining testing strategies [10, 16].

A major drawback of rRT-PCR for the detection of SARS-CoV-2 remains its suboptimal sensitivity and the absence of an absolute quantitative evaluation of SARS-CoV-2 viral load [12, 16]. By using digital droplet PCR (ddPCR) as gold standard (lower detection limit of 10 copies) to evaluate the performance of a rRT-PCR set at 38 cycle threshold (Ct) for positivity, the sensitivity reported by Yu *et al*. was substandard (~68%) [12] and similar to sensitivity reported by Zhao *et al*. (~67%) [16]. Interestingly, the Ct of qRT-PCR appears to be highly correlated with the copy number of ddPCR for both the ORF1ab (R2 = 0.83) and the nucleocapsid (R2 = 0.87) genes, while only 61.2% of single-gene positive samples on qRT-PCR were also detected on ddPCR (viremia ranging from 11.1–123.2 copies) [12]. In the frame, we also applied an in-house ddPCR assay targeting RdRp for SARS-CoV-2 detection on negative swabs after RTPCR. This developed assay accurately identified and quantified SARS-CoV-2 even at 2.9 copies per reaction (i.e. 28 viral copies/mL), thus suggesting an excellent analytical sensitivity. Moreover, as quantification per mL is highly dependent on the quality of sampling and extraction procedure, this assay includes an internal reference gene (RNAseP) for quality control. The presence of this reference gene excludes any eventual PCR inhibition and confirms successful RNA extraction, thus reducing substantially the risk of false negative results. Moreover, ddPCR will allow a linear quantitation of SARS-CoV-2 viral load, and the determination of viral load in clinical samples will henceforth supports an indepth interpretation of laboratory assays, which in turn will strengthen the strategy for case isolation, tracking and contact tracing. It is becoming common to assume that the Ct values from RT-PCR diagnostic tests are direct estimates of viral load and Ct values could serve in identifying non-infectious patients in spite of positive PCR or infectious samples in correlation to cell cultures. Even though using the Ct values as estimates of SARS-CoV-2 viral loads appears simple and routinely acceptable, it could be misleading and the risk of introducing errors might be consistent. Thus, using ddPCR at a second diagnosis level could help in an accurate quantitation of SARS-CoV-2 viral load and an appropriate management of SARS-CoV-2 positivity [12].

#### Validation of existing SARS-CoV-2 antigen and serological assays could enhance case-finding and surveillance of COVID-19 in sub-Saharan Africa

The limited laboratory capacity for SARS-CoV-2 molecular testing and the global stock-outs of reagents raised interest on using rapid and/or easy-to-use devices to facilitate screening in SSA, based either on SARS-CoV-2 antigen detection in sputum/throat/swab samples, or human antibodies detection in blood/sera/plasma specimens [17, 18]. However, the performance of these rapid assays remains largely unknown within SSA populations. Rapid antigen tests are designed to detect the presence of a viral antigen (targeting usually the Nucleocapsid), and the tests are inexpensive, easy to use, have short turn-around time, suitable for point-of-care (PoC), but with a lower diagnostic sensitivity (provide reliable results only with high viral-loads ≥100,000 copies/mL) especially during the first days after symptoms onset [19–21]. Due to this limitation, WHO, CDC and ECDC recommend the use of rapid antigen tests with a subsequent confirmation of negative results by RT-qPCR [22–24]. Among the 3rd generation antigen-detecting tests LumiraDx, Panbio COVID-19 Abbott Ag Rapid Test and Standard Q COVID-19 Ag Test Biosensor comply with the minimum performance requirements of the WHO [23].

Regarding serological assays, performance varies according to manufacturers (https://www.fda.gov/medical-devices/coronavirus-disease-2019-covid-19-emergency-use-authorizations-medical-devices/eua-authorized-serology-testperformance); FDA recommended antibody tests with highest performance are Abbott Architect SARS-CoV-2 IgG (100% sensitivity, 99.6% specificity), Abbott Laboratories Advise Dx SARS-CoV-2 IgM (95.0% sensitivity, 99.6% specificity), Assure Tech. Assure COVID-19 IgG/IgM Rapid Test Device (100% sensitivity for IgM and 90.0% for IgG; 98.8% specificity for IgM and 100% for IgG) and the EUROIMMUN SARS-COV-2 ELISA IgG (90.0% sensitivity and 100% specificity). Among them, Abbott ARCHITECT SARS-CoV-2 IgG assay showed a satisfactory performance, with excellent sensitivity and specificity after 14 days of sympthom onset [25–27]. The availability of neutralizing antibody detection kit, such as the approved GenScript cPass SARS-CoV-2 Neutralization Antibody Detection Kit (100% sensitivity and specificity) allows the discrimination of neutralizing antibodies at population level [26, 27].

Validation of these SARS-CoV-2 RDTs in SSA populations/settings is of paramount importance for optimal clinical use and positioning. On one hand, antigens are expressed only when the virus is actively replicating (greater performance during acute/early infection), while false-positive results could occur if strips recognize viral antigens from other human-coronaviruses [17]. Thus, validating the use of antigen RDT would reduce events of false negative-results, ensure rapid identify of cases, and minimise the need for expensive molecular testing [17]. On the other hand, COVID-19 antibody-tests might be convenient mainly during recovery as antibody response often occur in the second week post-infection or immunisation. Consequently, antibody testing might lead to delayed clinical-intervention or transmission-prevention [28, 29]. Moreover, COVID-19 antibody test might have cross-reactivity with other human-flu and/or coronaviruses, and the strength/breath of antibody response might vary with age, nutritional status, disease-severity, therapeutic-interventions, or infections like HIV or immunodeficiency-associated comorbidities [30]. Using an enzyme-linked immunosorbent assay (ELISA), Zhao *et al*. showed high rates of seroconversion based on total antibody (93%), IgM (83%) and IgG (65%), with seroconversion time ranging from 11–14 days [11]; the presence of antibodies rapidly increased to 100% (total antibody), 94% (IgM) and ~80% (IgG) as from 15 days after symptoms onset. These are consistent with evidence from Tan *et al*., revealing that anti-nucleocapsid-IgM starts on day-7 and peaks on day-28, while IgG ranges from day-10 to day-49 [11]. Interestingly, combining RNA and Antibody testing might improve the overall sensitivity for detecting COVID-19 case, pending confirmatory findings in real-life situations [11].

With scarcity of data as of April 16, 2020 within the African populations/settings, WHO does not recommend the use of these rapid tests for patient care, but strongly encourages research on the potential diagnostic utility of antigen-detecting rapid tests and the continuation of work to establish the usefulness of COVID-19 antibody testing in case management and in epidemiological surveillance [31]. Such evidence would inform global policy on the use of immunodiagnostic rapid tests, and on specific conditions/settings where such tests can be useful for clinical decision, epidemiologic understanding, and/or infection control without referring to molecular assays [28, 29, 31].

### Research hypotheses

Research on COVID-19 diagnostic approaches will integrate and improve the available infrastructure, methodologies, and expertise on COVID-19 in Cameroon and other SSA countries;Evidence on the performance of real-time PCR devices in the clinical diagnosis of SARS-CoV2 in SSA would help in identifying the most efficient platforms and in adapting result interpretation according to cycle threshold (Ct) for confirmation of COVID-19 in SSA settings;Evidence on the performance of COVID-19 rapid diagnostic tests would help in identifying the most reliable assays and in designing the most suitable algorithm for use of rapid tests in clinical management and in epidemiological surveillance of COVID-19 in SSA settings;Evaluating the sensitivity of a combination of nucleic acid and RDT would significantly improve the efficiency in detecting COVID-19, both in the even and late phases of infection.

### Study objectives

#### Main objective

With the goal to support public health measures for prevention and control of COVID-19 infections in Africa, our study aims at evaluating the diagnostic performance of molecular tests and serological rapid kits for the detection of SARS-CoV2 among individuals tested for COVID-19 in the Cameroonian context.

### Specific objectives

**To integrate and improve the available infrastructure, methodologies, and expertise on COVID-19**. For this purpose, we will create a platform enabling researchers and clinicians to better integrate and coordinate their research and translate the project outcomes into scientific and clinical expertise for the management of COVID-19 infection within the African context;**To enhance the capacities of the involved centers in Cameroon to screen and detect individuals at risk for COVID- 19 infection, by putting in place effective screening mechanisms and facilities at core sites (based on molecular and serological detection methods and SARS-CoV-2 genome sequencing)**. In this frame, individuals will be considered at risk of COVID-19 infection according to surveillance case definition for human infection with novel coronavirus published by WHO [WHO/COVID-19/Surveillance/v2020.2, January 15 2020];**To determine the performance of sensitive and specific point-of-care molecular detection assay for SARS-CoV-2**. Previous data on Zaire Ebola virus suggested that the POC molecular test has comparable diagnostic accuracy to the conventional real-time, minimized the time to obtain a result, thereby allowing clinicians or public health staff to make expeditious decisions. In the COVID-19 case, nasopharyngeal and oropharyngeal swab, and saliva will be valid samples to obtain a rapid and non-invasive screening for all travelers arriving in Cameroon. Concordance with other molecular tests already available for COVID-19 will be assessed (Corman et al. 2020; Chu et al. 2020);**To apply a rapid and sensitive ddPCR-assay SARS-CoV-2 quantification method as complementary to the standard RTPCR for COVID-19 diagnosis**. This test (single-step ddPCR assay) will have the ability to detect SARS-CoV-2 genome at very low copies number, representing a chance to detect infected subjects before any symptom onset, and to reveal the presence of COVID-19 in the environment in close contact with infected individuals. Based on ddPCR, a linear evaluation of SARS-CoV-2 load will be also available;**To validate a large panel of serological assays to identify COVID-19-exposed or vaccinated persons and to follow-up of COVID- 19 convalescents or immunisation**. This panel will enable an appraisal of Nucleocapside (N) and Spike protein (S) used in screening for natural and artificial immunity respectively;**To evaluate the variability of circulating SARS-CoV-2 variants in Cameroon based on whole genome sequencing and phylogenetic approaches**. Through sequencing of SARS-CoV-2, evidence on the dynamics of COVID-19 from the lineage of origin to newly emerging variants will be delineated, with the goal in predicting the trends of SARS-CoV-2.

## Methods

### Study design

**Study type and population**: Prospective, cross-sectional, observational study among indivividuals in Cameroon;

**Study sites**: The Chantal BIYA International Reference Centre (CIRCB) is the reference study site for the project, in connexion with the routine national laboratories network for COVID-19 testing in the country [4], as per the national guidelines (Fig 1).

**Fig 1 pone.0273818.g001:**
[figure not shown]
Network for COVID-19 testing laboratories. COVID-19: Coronavirus Disease 2019.

#### Description of the Cameroonian settings

In response to COVID-19, Cameroon has developed a national guideline for COVID-19 prevention and control in the country. This guideline entails case definition, case notification, clinical diagnosis of COVID-19, laboratory diagnosis of SARS-CoV2, case management of COVID-19, surveillance strategies at entry points and at the health facilities, triage approaches, etc. Based national response, 4,982 samples have been tested from suspects for 1,016 (20.39%) confirmed SARS-CoV2 positive by real-time qRT-PCR. Majority is from the political capital region of Yaoundé (558), followed by the economical capital region of Douala (381); male/female sex ratio is 3/2 with a median of 39 (min-max: 0–81) years old; the case fatality rate (CFR) is 2.00% (22) for 16.27% recovery rate (https://www.worldometers.info/coronavirus/). Apart from travellers for whom a conventional real-time polymerase chain reaction (rt-PCR) test is required, testing for COVID-19 is performed by using the antigen rapid detection test (RDT) as the screeining tool, and eventually followed by a PCR if negative antigen RDT in a person with suspicion of COVID-19 symptom or a high-risk contact, as per the national guidelines, as shown in Fig 2 [4].

**Fig 2 pone.0273818.g002:**
[figure not shown]
Standard algortihm for routine COVID-19 testing in Cameroon. COVID-19: Coronavirus Disease 2019.

**Study reference site: Virology Laboratory of CIRCB** (http://www.circb.cm/btc_circb/web/) The “Chantal BIYA” International Reference Center for research on HIV/AIDS prevention and management (CIRCB) is a government institute of the Ministry of Public Health established on February 2006, of conducting research and clinical monitoring of HIV and co-infections/comorbidities, with compliance to QC/QA and proficiency testing. CIRCB is a WHO-Candidate as National HIV Drug Resistance Reference laboratory, providing technical support for viral-sequencing (PHIA survey, etc) and training of health-professionals. CIRCB has a biobank dedicated for the storage of well characterised infectious samples collected from heath facilities and within research projects, in accordance with GCP and ethical regulations. The standard operational procedures (SOP) for the biobanking are available at www.circb-cm/LBIOSOP-English (English version) and www.circb-cm/LBIOSOP-French (French version). Samples collected are plasma, serum, buffy-coat, blood, DNA, RNA, proteins, PBMCs, tissues, smears, saliva/sputum, infectious pathogens (HIV, HBV, HCV, HPV, etc). In response to COVID-19, CIRCB is a reference laboratoriy for SARS-CoV2 testing, a member of the National COVID-19 public health operations centre, a member of the national COVID-19 genomic surveillance plateform, and a member of the scientific taskforce for COVID-19 in the country.

**Study duration**: The study will run for a duration of two years, with an active enrolment phase during the first 6 months of the project, and subsequent laboratory analyses.

**Sampling method**: A consecutive non-randomised sampling strategy will be used for participants enrollment;

**Target population**: Individuals visiting our routine sample collection site for COVID-19 screening within the framework of the established laboratory network in place, CIRCB being the study reference laboratory.

### Eligibility criteria

**Inclusion criteria**: Every individual found in Cameroon at the moment of the study, suspected/contact COVID-19 case as defined by the WHO, aged 21 years and above, and provide a written informed consent for participation;

**Non-inclusion criteria**: Suspected case without clinical data, any suspected case managed out of the country guidelines, or any suspected case without blood/respiratory fluid specimen available;

**Exclusion criteria**: Enrolled participant with neither results of real-time PCR, serological testing, nor SARS-CoV2 sequence data following positive-PCR for the respective analysis.

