#### Molecular testing of COVID-19

Molecular testing entails conventional real-time PCR, point-of-care GeneXpert Express (Cepheid), ddPCR as well as sequencing reactions. For all molecular testing and sequencing, viral RNA was extracted from respiratory samples using the QIAmp viral RNA Mini kit (Qiagen Hilden, Germany) according to the manufacturer’s protocol.

*Real-time qRT-PCR for SARS-CoV2 testing*. This protocol is designed to detect SARS-CoV2 in human clinical specimens. The two monoplex assays are reactive with the 2019 novel coronavirus, considering: (1) the genetic diversity of 2019-nCoV in humans and animals, (2) the use of an internal control, (3) the kit being widely available across SSA. Amplification will be performed on Applied Biosystem/Thermocycler devices (TheromFisher, ViiATM 7 Real-Time PCR), with a positive control, primer sets, primer and probe sequences. The amplicon sizes of Assay 1 and Assay 2 are 132 bp and 110 bp, respectively. Interpretation of positivity of N gene RT-PCR and Orf1ab is done at required cycle thresholds (Sun Yat-sen University protocol). A negative N gene positive/Orf1b refers to the absence of SARS-CoV2. Results will be evaluated with reference to ddPCR.

*GeneXpert for SARS-CoV2 testing*: *Xpert*^*®*^
*Xpress SARS-CoV-2*. Xpert^®^ Xpress SARS-CoV-2 is a test that has the Food and Drug Administration (FDA) emergency use authorization (EUA). Xpert^®^ Xpress SARS-CoV-2 is currently the most prominent test for real-time RT-PCR rapid test for SARS- CoV-2 developped by Cepheid, which provides results in just 45 min using GenXpert benchtop system. It is a rapid and automated point-of-care (POC) molecular test that enables the qualitative detection of SARS-CoV-2 in nasopharyngeal swab, nasal wash, or aspirate specimens from COVID-19 suspects. The test requires only a minute for sample preparation, employs cartridges, and targets multiple regions of the viral genome. Accuracy will be evaluated using ddPCR as gold standard.

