#### Statistical analysis

Data will be collected on standard tools (S3 File) by trained field epidemiologists and stored in a password-protected database to ensure confidentiality of participant data and their privacy at the local institution in Yaoundé-Cameroon, by experienced statisticians who will coordinate data management and analyses using SPSS software, according to Good Clinical Data Management Processes (GCDMP).

Diagnostic Performance will be evaluated regarding the sensitivity, specificity, positive/negative predictive values (with 95% Confidence Intervals) will be described using ddPCR as molecular gold standard assay (lower detection limit of 10 copies/test) and ELISA as serology gold standard, stratified by range of viral loads, Ct values, duration after symptom onset, target biomarkers and viral diversity. To provide the highest level of evidence, adjustments of confounders (age, gender, HIV status, onset of symptoms, site, etc) will be performed using logistic and linear regression, wherever applicable.

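### The post-enrolment exclusion is ambiguously worded and, read per analysis, may remove failed index tests from the accuracy tables, so reported performance may be overstated

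*Protocol article*

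**What the plan says.** The Eligibility criteria section has two relevant rules. Before enrolment, the non-inclusion criteria already turn away "any suspected case without blood/respiratory fluid specimen available". After enrolment, the exclusion criterion removes an "Enrolled participant with neither results of real-time PCR, serological testing, nor SARS-CoV2 sequence data"; the full sentence, with its closing words, is "Enrolled participant with neither results of real-time PCR, serological testing, nor SARS-CoV2 sequence data following positive-PCR for the respective analysis".

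The Statistical analysis section states that "sensitivity, specificity, positive/negative predictive values (with 95% Confidence Intervals) will be described using ddPCR as molecular gold standard assay", with "ELISA as serology gold standard". Under Molecular testing of COVID-19, conventional real-time PCR and Xpert are both to be judged against ddPCR. That section also lists, among the features of the real-time PCR protocol, "the use of an internal control". Expected outcomes adds overall agreement to the accuracy measures. Research hypotheses says the evidence should identify the most efficient platforms and the most reliable rapid assays.

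**The concern.** An accuracy table needs a reference result to place a participant in the diseased or non-diseased column. A missing reference result is therefore a sound reason to leave the table. A missing index result is different: if the test was tried and failed, the failure is part of how the test performs.

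The exclusion names real-time PCR and serology, which are largely index tests here, and it does not name ddPCR, the molecular reference. Read per analysis, it conditions accuracy on the index test having produced a result. An assay that fails often would lose its failures from view, and assays would be compared on different subsets of participants. That matters because the study is meant to select platforms and kits for field use, where a run with no valid result is a case not identified by that run.

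**Working it through.** **1. What the sentence can mean.** The neither–nor construction, taken literally, requires all three result types to be missing. The closing reference to the respective analysis has no work to do on that reading; it makes sense only if the rule operates analysis by analysis. To see what each reading removes, take the planned 1,536 participants (Sample size section) and an assumed no-result rate f per test.

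| f (assumed) | Literal, all three missing, independent: 1,536 × f³ | Per analysis: 1,536 × f |
|---|---|---|
| 2% | 0.01 | 31 |
| 5% | 0.2 | 77 |
| 10% | 1.5 | 154 |

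The literal rule would do almost nothing.

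**2. Why invalid runs are likely to be among those removed.** Participants without a specimen are stopped before enrolment. The real-time PCR protocol has an internal control, so a run can be invalid. The article gives no category for an invalid result. An invalid run therefore most naturally counts as having no result. This is an inference from the text, not a statement in it.

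**3. Effect on sensitivity.** With exclusion, the estimate is Se = TP/(TP + FN) among valid results. With failed attempts kept as not detected among reference positives, it is Se × (1 − f), so the gap is Se × f. This assumes f is unrelated to the result the test would have given. The document states no failure rate, so there is no plan figure to reproduce. Illustrative sensitivities: 68% is the article's cited figure for rRT-PCR against ddPCR, 75% and 98% are the ends of its range for the pre-selected serological tests, and 90% lies between.

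| Se among valid | f = 2% | f = 5% | f = 10% |
|---|---|---|---|
| 68% | 66.6% | 64.6% | 61.2% |
| 75% | 73.5% | 71.25% | 67.5% |
| 90% | 88.2% | 85.5% | 81.0% |
| 98% | 96.0% | 93.1% | 88.2% |

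The gap runs from 1.4 to 9.8 points. Two assays both at 90% among valid results, failing 2% and 10% of the time, differ by 88.2 − 81.0 = 7.2 points among all attempted. Exclusion would show them as equal.

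**4. Size against sampling error.** At Se 90%, the 95% half-width 1.96 × √(0.9 × 0.1/n) is 2.1 points with n = 783 reference positives (1,536 × 51%, the sample-size assumption). It is 3.3 points with n = 313 (1,536 × 20.39%, the national positivity quoted in the description of the Cameroonian settings). A 4.5-point gap at f = 5% exceeds both; a 1.8-point gap at f = 2% exceeds neither.

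**5. Bias against what the test would have shown had every run worked.** Let failure rates differ between would-be true positives and would-be false negatives, at Se 68%:
- 5% and 5%: 68.0%, no bias.
- 2% and 10%: 0.68 × 0.98 / (0.68 × 0.98 + 0.32 × 0.90) = 69.8%.
- 10% and 2%: 0.68 × 0.90 / (0.68 × 0.90 + 0.32 × 0.98) = 66.1%.

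Against this target the direction is not fixed.

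**6. Specificity.** Take Sp 98% among valid results and f = 5%. Counting failures as not correctly classified gives 0.98 × 0.95 = 93.1%. Counting them as not detected, and so as negatives, gives 93.1% + 5% = 98.1%, slightly above the conditional figure. The scoring rule has to be set separately for reference negatives.

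**The case against.** A reader might infer that the article orders failed and invalid tests to be discarded and that performance is therefore overstated. The documents do not support that. The exclusion is stated; the treatment of invalid runs is not. Repeat testing or an invalid category may sit in the full protocol, laboratory procedures or analysis plan, none of which is shown, and their absence from an article is no fault. Nor is the direction of bias settled: accuracy among valid results, reported beside a failure rate, is a legitimate target, and against it exclusion may bias up, down or not at all.

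The scope is also narrower than it may seem. The rule does not name antigen tests, and its sequencing clause does not touch accuracy denominators. Serological testing can include ELISA, the serology reference, and exclusion for a missing ELISA result is proper. A missing result may mean the test was never run: under the routine algorithm, PCR follows a negative antigen test only in some people. Such participants should not be scored as assay failures. The RNAseP control in the introduction is no evidence here either, since it belongs to ddPCR, the molecular reference.

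All of this stands, and it limits the claim. It does not remove it. The article publishes an exclusion conditioned on results of tests under evaluation, and the only reading that gives its closing words a function is per analysis. An analysis plan that kept such participants would have to depart from that criterion.

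**Conclusion.** The point holds as a fault in a stated rule: the exclusion is ambiguous and, read per analysis, may overstate performance. An upward difference is certain only for sensitivity against a denominator of all attempted tests, and only if invalid runs count as having no result. Its size is then about Se × f, for example 4.5 points at Se 90% and f = 5%. The 2% to 10% range for f is assumed throughout, and failures are taken as unrelated to the would-be result. The fair comparison of assays is what is most exposed, because equal figures among valid results can hide different failure rates. It should be corrected, but it does not by itself undermine the study.

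**What to change.** Reword the exclusion so that each accuracy analysis leaves out only participants with no reference result (ddPCR for the molecular comparisons, ELISA for serology) or on whom the index test was never attempted. State what counts as no result. Keep attempted index tests that remain failed or invalid after any repeat the protocol allows.

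For each assay, report the number and rate of such failures with a 95% confidence interval. Give sensitivity and specificity twice: among valid results, and with failures counted as not correctly classified (not detected among reference positives, not a true negative among reference negatives). Apply the same rule to Xpert and the antigen tests, which the present sentence does not name.

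The cost is a rewritten sentence, a laboratory record that separates not attempted from attempted without a valid result, and a few more table columns. Some assays will show slightly less favourable figures.
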